## Methods and analysis

### Study design

The PUSH is a real-world, 4 week prospective, three-arm observational study of patients with established ASCVD or high cardiovascular risk with and without T2D undergoing regular exercise therapy during inpatient rehabilitation in a single center in Switzerland. Employing a multi-group design and a two-step analytic approach, the study investigates the changes in physical performance (and glycemic control) in 3 categories of glycemic control after 4 weeks. Furthermore, the associations between the 3 categories of glycemic control and new guideline directed antidiabetic treatment (inadequate glycemic control and diabetes + new SGLT2i vs. adequate glycemic control and diabetes vs. no diabetes) with physical performance are evaluated in cross-sectional and prospective analyses. A flow chart of the study is shown in Figure 1.

**Figure 1 F1:**
[figure not shown]
Flowchart of the PUSH study. ASCVD, atherosclerotic cardiovascular diseases; CV, cardiovascular; T2D, type II diabetes mellitus; FPG, fasting plasma glucose; SGLT2i, sodium glucose cotransporter 2 inhibitor.

#### Eligibility criteria

All consecutive patients with established ASCVD or high cardiovascular risk with or without T2D who met the inclusion criteria summarized below were prospectively enrolled as from 1 January 2018 and data collection lasted until 30 September 2020. Individuals below 40 years of age upon admission were excluded due to the low incidence of ASCVD in people under 40 years (32). For participants with T2D, T2D was determined by self-report with verification of medical records, current treatment or FPG ≥ 7 mmol/L and symptoms of hyperglycemia with random plasma glucose ≥ 11.1 mmol/L (33). Individuals who had a clinical history strongly suggestive of type I diabetes were excluded.

#### Inclusion criteria

Ambulatory patients, defined as able to walk about and not bedridden, with or without walking aids admitted following a medical or surgical condition warranting inpatient rehabilitation,willing to give informed written consent,with established ASCVD or high cardiovascular risk with and without T2D were included. ASCVD and high cardiovascular risk were defined as follows:

a. established ASCVD: coronary artery disease (CAD), cerebrovascular disease (CeVD), peripheral artery disease (PAD) and ischemic congestive heart failure (CHF),b. high cardiovascular risk: as defined in the 2016 European Guidelines on cardiovascular disease prevention in clinical practice (13). consisting of patients without clinically manifest ASCVD with markedly elevated single cardiovascular risk factors (hypertension with blood pressure ≥180/110 mmHG, blood lipid profile with cholesterol > 8 mmol/L, metabolic syndrome and central obesity with body mass index ≥40 kg/m^2^ in patients below 60 years of age), or with T2D plus any additional risk factor, or with moderate chronic kidney disease defined as glomerular filtration rate between 30 and 59 mL/min/1.73 m^2^, or with a calculated systematic coronary risk estimation (SCORE) ≥5 and <10 % (13), or with scores above the high risk cut-off using the American College of Cardiology (ACC)/American Heart Association (AHA) score of ≥20% (34, 35).

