Given this background, the main aims of this study are firstly, to investigate the changes in physical performance and glycemic control 4 weeks after initiation of guideline-directed medical therapy of an SGLT2i and exercise therapy in patients with established ASCVD or high cardiovascular risk and T2D with initial inadequate glycemic control; secondly, to investigate the changes in physical performance and glycemic control 4 weeks after exercise therapy only in patients with established ASCVD or high cardiovascular risk and T2D with adequate glycemic control; thirdly, to investigate the changes in physical performance 4 weeks after exercise therapy only in non-diabetic patients with established ASCVD or high cardiovascular risk; and fourthly to investigate the cross-sectional and longitudinal association of glycemic control at baseline and new guideline directed antidiabetic treatment (inadequate glycemic control and diabetes + new SGLT2i vs adequate glycemic control and diabetes vs. no diabetes) with physical performance and other outcomes influencing physical performance (secondary outcomes), in patients with established ASCVD or high cardiovascular risk after adjusting for baseline covariates.

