### Study group categories

Glycemic control was assessed within the first 3 days upon admission by measurement of fasting plasma glucose (FPG) with the widely used diagnostic cut-off of ≥7 mmol/L employed to define inadequate glycemic control (33, 36). Hemoglobin A_1c_ (HBA_1c_) testing was equally done in all participants upon admission but was not used to define inadequate glycemic control in this cohort to circumvent the bias linked to participants with conditions that affect erythrocyte turnover such as acute bleeding and/or erythrocyte transfusion during the acute hospitalization prior to rehabilitation (33). HbA_1c_ was however used as one of the parameters to distinguish participants with diabetes or impaired glucose metabolism from those with normal glucose metabolism as described below.

Depending on their glycemic control upon admission and following guideline recommendations, participants were categorized to one of three groups using clinically defined cut-off categories of FPG levels as follows (11):

Group I: Participants with inadequately controlled T2D defined as mean FPG of ≥7 mmol/l within the first 3 days upon admission under other standard of care medication, who were afterwards administered *de novo* SGLT2i treatment; namely either canagliflozin 100 mg, or dapagliflozin 10 mg, or empagliflozin 10 mg once daily, with the choice of which of the SGLT2is being at the discretion of the individual treating physician,

Group II: Participants with adequately controlled T2D, previous diagnosis of T2D or use of antidiabetic medication, with mean FPG <7 mmol/L; and participants with impaired fasting glycemia (IFG) or pre-diabetes, defined as mean FPG of 5.6–6.9 mmol/L and HbA_1c_ levels of 5.7–6.4 % (15, 33), under other standard of care treatment and no SGLT2i,

Group III: Participants with no previous diagnosis of T2D or use of antidiabetic medication and normal glucose metabolism defined as FPG of ≤ 5.5 mmol/L under other standard of care treatment and no SGLT2i were included as a reference group as previously described in the meta-analysis of prospective studies on diabetes mellitus, FPG, and risk of vascular disease (11).

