#### Data analyses

Demographic data will be examined using independent-samples *t*-tests and Fisher's exact tests for dichotomous variables. Independent-samples *t*-tests and repeated-measures ANOVAs will be employed to compare changes in physical performance after 4 weeks. Differences between primary and secondary outcome variables after 4 weeks will also analyzed by linear mixed-effects models (LMMs). The time factor for the model will be set at baseline and week 4. The models will include model-based adjustments for baseline characteristics influencing physical performance in such cohorts: (1) age, sex, BMI, waist circumference, diabetes duration and history of cardiovascular disease.

To minimize the bias that could result from participants in the 3 groups having highly variable duration of stay, the prospective analyses will be performed on a modified intention-to-treat and per protocol basis. The modified intention-to-treat population will be defined as participants who have been categorized to a study group and have at least one follow-up measurement of the primary outcomes, regardless of treatment adherence or duration of stay. The “last observation carry-forward method” will be used in the absence of complete follow-up data. For “per protocol” analysis, only those participants who have follow-up measurements after a minimum treatment duration or length of stay of ≥20 days will be included.

Sensitivity analyses will be performed to account for potentially non-ignorable missing data due to dropout as well as the possible impact of other potentially influential variables. A Bonferroni correction will be applied to the LMM analyses of the primary and secondary outcomes.

Pre-specified subgroup analyses will be conducted; these will include subgroups defined according to the various entities of ASCVD, gender, age groups, and other factors.

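### One high-risk entry route is open only to participants with T2D, so contrasts with the no-diabetes reference group partly reflect different entry rules among participants without ASCVD

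*Protocol article*

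**What the plan says.** The Inclusion criteria section of the protocol article admits patients with established ASCVD or with high cardiovascular risk. The high-risk category has several routes:

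- "patients without clinically manifest ASCVD with markedly elevated single cardiovascular risk factors", with thresholds for blood pressure (≥180/110), cholesterol (>8 mmol/L), and metabolic syndrome with BMI ≥40 under age 60;
- "or with T2D plus any additional risk factor";
- "or with moderate chronic kidney disease defined as glomerular filtration rate between 30 and 59";
- SCORE of at least 5% and below 10%, or an ACC/AHA score of at least 20%.

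The Exclusion criteria section removes lower risk categories.

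Under Study group categories, Group III has no T2D diagnosis, no antidiabetic medication and normal glucose metabolism. Its members "were included as a reference group as previously described in the meta-analysis of prospective studies on diabetes mellitus, FPG, and risk of vascular disease". Group II combines adequately controlled T2D with impaired fasting glycemia or pre-diabetes.

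The fourth aim in the Introduction is a cross-sectional and longitudinal comparison of "inadequate glycemic control and diabetes + new SGLT2i vs adequate glycemic control and diabetes vs. no diabetes". The Data analyses section plans t-tests and repeated-measures ANOVAs with no stated covariates, and mixed models adjusted for "age, sex, BMI, waist circumference, diabetes duration and history of cardiovascular disease".

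**The concern.** The exposure under study is part of the rule that admits people to the cohort. Take two patients without ASCVD who share one ordinary risk factor and meet no other high-risk criterion. The one with T2D is eligible; the one without is excluded. Group III therefore has no counterpart to this kind of T2D participant.

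If these entrants differ from the rest in walking distance or in 4-week gain, part of any difference between the T2D groups and the reference comes from the entry rule rather than from diabetes, glycemic control or new SGLT2i treatment. The pre-diabetic part of Group II lacks the same route, so Group I against Group II is also touched, though less.

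**Working it through.** **Step 1. Routes open to each group.**

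| Entry route | T2D (Group I, most of II as named) | Pre-diabetes (part of II) | Group III |
|---|---|---|---|
| Established ASCVD | open | open | open |
| Extreme single factor | open | open | open |
| GFR 30–59 | open | open | open |
| SCORE 5 to <10%, or ACC/AHA ≥20% | open | open | open |
| T2D plus one further risk factor | open | closed | closed |

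The rule for Group III is strictly narrower. The difference acts only on participants without ASCVD who also miss every other high-risk route.

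**Step 2. What the planned analyses remove.** The t-tests and ANOVAs state no covariates. In the mixed models, cardiovascular history handles ASCVD present or absent. Age, sex, BMI and waist circumference absorb part of what remains. Blood pressure, lipids, kidney function and risk score, which define most of the non-diabetes routes, are not listed. Diabetes duration has no variation in Group III, so it cannot balance that group against the others.

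**Step 3. Scale.** The plan states no figure to reproduce, and the article gives no case mix. The following inputs are assumptions:

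- h, share of T2D participants without ASCVD: 10–50%;
- q, share of those who qualify only by the T2D route: 30–70%;
- d, difference in 4-week gain between these entrants and other T2D participants: 10 or 20 m, either sign.

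Share without a counterpart: s = h × q, from 0.10 × 0.30 = 3% to 0.50 × 0.70 = 35%. Midpoint for h of 35% and q of 50%: 17.5%.

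Shift in a contrast between a wholly T2D group and Group III: s × d.

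The Sample size section gives an SD of 40 m for the gain and 130 per group. The standard error of an unadjusted difference is 40 × √(2/130) = 4.96 m. The rejection rate with no true difference is P(|Z + s·d/4.96| > 1.96).

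| h | q | s | size of d | shift | rate at nominal 5% |
|---|---|---|---|---|---|
| 10% | 30% | 3% | 20 m | 0.6 m | 5.2% |
| 20% | 30% | 6% | 20 m | 1.2 m | 5.7% |
| 10% | 70% | 7% | 20 m | 1.4 m | 5.9% |
| 35% | 50% | 17.5% | 10 m | 1.75 m | 6.4% |
| 35% | 50% | 17.5% | 20 m | 3.5 m | 10.9% |
| 50% | 70% | 35% | 20 m | 7.0 m | 29.2% |

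The shift takes the sign of d; the rate is the same for either sign. For comparison, 15% of the anticipated 80 m gain is 12 m. The article does not state the base for its 15%, so 12 m is itself a reading.

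**Step 4. Baseline contrast.** With SD 88 m (the community cohort cited under Sample size), 150 per group and an assumed 40 m difference in level, the standard error is 88 × √(2/150) = 10.16 m. For s of 6%, 17.5% and 35%, the shifts are 2.4, 7.0 and 14 m, with rates of 5.6%, 10.6% and 28.1%.

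**Step 5. Group I against Group II.** If a share p of Group II is pre-diabetic and s is equal among T2D members of both groups, the shifts are s·d in Group I and (1 − p)·s·d in Group II. The net shift is p·s·d, smaller than against Group III. The article does not give p.

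**The case against.** The strongest defence is that the cohort is defined by cardiovascular risk category, taken from a guideline in which T2D counts towards risk, with lower categories excluded from every group. On that view the groups are already aligned, and aligning them on non-diabetes risk is a different comparison. This stands as a reason to keep the full-cohort contrast. It does not make that contrast one between groups alike except for diabetes and its treatment.

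The defence also limits the point in several ways:

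- The route needs a further risk factor. A reader might infer that diabetes alone admits a patient; the criterion does not say so.
- Patients are admitted after a condition warranting inpatient rehabilitation, and the planning pilot was in cerebrovascular disease. A low share without ASCVD is plausible, and the effect would then be small.
- The sign for 4-week gain is open. Planning runs from a 250 m baseline to a 344 m target, so lower-burden entrants might start nearer the target and gain less.
- The mixed models adjust for several related variables and carry a Bonferroni correction. Percent-predicted distance standardises for age, sex, height and weight.
- The first three aims are within-group changes and do not use Group III as a comparator.

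The limitations discuss non-randomization and selection by glycemic control, and Data analyses promises sensitivity analyses for other influential variables. Neither names the entry rule or commits to examining it.

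**Conclusion.** The asymmetry follows directly from the eligibility and group definitions. The planned analyses remove it only in part, and the stated limitations do not mention it.

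Its size is unknown. Under the assumptions above, the shift in the 4-week contrast with Group III runs from under 1 m to about 7 m in either direction, against 12 m if the 15% is taken on 80 m. The 7 m end needs all three inputs to be high. The rejection rates apply only to unadjusted tests at nominal 5%. They do not describe the adjusted, Bonferroni-corrected mixed models.

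A reader might infer that Group III must look worse than a true no-diabetes counterpart, or that Group I must look better against it. The article does not support either for 4-week change, because it gives neither the case mix nor the gains by entry route. The point justifies an inexpensive sensitivity analysis and a sentence of disclosure. It does not show that the study's contrasts are wrong.

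**What to change.** Recruitment is complete, so eligibility cannot change, but the article still describes the analyses as to be done. Before they are run:

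1. Derive one flag per participant: whether an entry criterion is met without counting diabetes. Table 1 already schedules eligibility screening, medical history, smoking status, blood pressure, lipids and kidney parameters. If a risk score takes diabetes as an input, state how it is computed for this flag.
2. Report the flag by group, with the pre-diabetic and T2D parts of Group II shown separately. If the share entering only through the T2D route is trivial, this table settles the matter.
3. Prespecify a sensitivity analysis that repeats I against III, II against III, and I against II among flagged participants, beside the full-cohort contrasts.
4. State in the limitations that the full-cohort contrasts depend on an entry rule that uses diabetes.

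No new data are needed. The cost is fewer T2D participants in the restricted analysis. At the assumed extreme of 35%, 130 T2D participants become about 84.5. The standard error against 130 in Group III is then 40 × √(1/84.5 + 1/130) = 5.59 m instead of 4.96 m, about 13% wider. At 17.5% it is 40 × √(1/107.25 + 1/130) = 5.22 m, about 5% wider. The restricted analysis also describes a narrower T2D population than the aims do, which is why it should stand beside the full-cohort result and not replace it.

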#### Exclusion criteria

Patients who were not willing to give informed consent or declined suggestions of guideline directed medical therapy,who were not able to walk,in lower cardiovascular risk categories,had a history of unstable angina or acute myocardial infarction in the 4 weeks prior to baseline or any terminal cardiovascular, respiratory, musculoskeletal, or neurological condition that relevantly limited patient's physical performance and/or movement defined as 6-min walk distance of <25 m at baseline,had relevant pain limiting physical performance and/or movement defined as pain numeric rating scale (NRS) of above 5/10 at rest,had an active malignancy,had advanced renal disease defined as glomerular filtration rate (GFR) permanently below 30 mL/min/1.73 m^2^ in the 12 weeks prior to admission,were already under treatment with SGLT2i upon admission were excluded. Participants were considered already under treatment with an SGLT2i if they received continuous SGLT2i medication for longer than 3 days prior to admission.

### Study group categories

Glycemic control was assessed within the first 3 days upon admission by measurement of fasting plasma glucose (FPG) with the widely used diagnostic cut-off of ≥7 mmol/L employed to define inadequate glycemic control (33, 36). Hemoglobin A_1c_ (HBA_1c_) testing was equally done in all participants upon admission but was not used to define inadequate glycemic control in this cohort to circumvent the bias linked to participants with conditions that affect erythrocyte turnover such as acute bleeding and/or erythrocyte transfusion during the acute hospitalization prior to rehabilitation (33). HbA_1c_ was however used as one of the parameters to distinguish participants with diabetes or impaired glucose metabolism from those with normal glucose metabolism as described below.

Depending on their glycemic control upon admission and following guideline recommendations, participants were categorized to one of three groups using clinically defined cut-off categories of FPG levels as follows (11):

Group I: Participants with inadequately controlled T2D defined as mean FPG of ≥7 mmol/l within the first 3 days upon admission under other standard of care medication, who were afterwards administered *de novo* SGLT2i treatment; namely either canagliflozin 100 mg, or dapagliflozin 10 mg, or empagliflozin 10 mg once daily, with the choice of which of the SGLT2is being at the discretion of the individual treating physician,

Group II: Participants with adequately controlled T2D, previous diagnosis of T2D or use of antidiabetic medication, with mean FPG <7 mmol/L; and participants with impaired fasting glycemia (IFG) or pre-diabetes, defined as mean FPG of 5.6–6.9 mmol/L and HbA_1c_ levels of 5.7–6.4 % (15, 33), under other standard of care treatment and no SGLT2i,

Group III: Participants with no previous diagnosis of T2D or use of antidiabetic medication and normal glucose metabolism defined as FPG of ≤ 5.5 mmol/L under other standard of care treatment and no SGLT2i were included as a reference group as previously described in the meta-analysis of prospective studies on diabetes mellitus, FPG, and risk of vascular disease (11).

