### Outcome measures: Assessment, blinding, and rationale

The PUSH assessed objective and subjective outcomes of physical performance in addition to hemodynamic, cardiorespiratory, and cardiometabolic risk variables. Outcome assessments were done upon admission (baseline), facultatively at week 2 and at week 4 (Table 1). All participants, direct care providers and assessors were masked to the outcomes under investigation throughout the study. Whereas, participant and care providers were blinded by categorically withholding supplementary information on the glycemic control categories described above and exposures under investigation, main outcome assessors (therapists and laboratory technicians) were masked by complete prohibition of access to patient medication data as per previously established institutional policy.

**Table 1 T1:** Assessment time plan.

**Assessment**	**Time points during study**		
	**Baseline** ^a^	**Week 2**	**Week 4**
Screening for inclusion and exclusion criteria	°		
Participant characteristics^b^	°		
Status of medications^c^	°	°	°
Anthropometric and clinical parameters^d^	°	°	°
Laboratory tests^e^	°	°	°
Rehabilitation outcomes^f^	°	°	°
Transthoracic echocardiography^g^	°		°
Sonographic assessment of liver parenchyma (NAFLD)^h^	°		°
Muscle sonography^i^	°	°	°
Monitoring for adverse events^j^	Throughout stay		

a *Baseline was defined as the date of eligibility confirmation and inclusion in the study. If no data were available at baseline, the most recent data from the hospitalization prior to admission were used*.

b
*Included information on age, sex, medical history, complications and comorbidities, smoker status, coffee consumption.*

c
*Included antidiabetic agents, antihypertensives, lipid-lowering drugs, thrombocyte aggregation inhibitors, therapeutic anticoagulation, use of proton pump inhibitors, uric acid lowering drugs, antidepressants, opiates, NSAIDs, neuropathic pain treatment, vitamin D, iron, calcium, and magnesium substitution.*

d
*Included body weight, BMI, waist and hip circumferences, estimation of skeletal muscle mass in kg using the Baumgartner equation, mean systolic and diastolic blood pressures, mean fasting plasma glucose (for all groups at baseline, for group I and II at week 2 and 4), peak expiratory flow rate, state of nocturia, pain numeric rating scale [NRS] (range 1–10).*

e

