*Included hemoglobin, thrombocyte count, magnesium, ionized calcium, ferritin, transferrin saturation, albumin, lipid profile (total cholesterol in mmol/L, mean HDL-Cholesterol in mmol/L, mean LDL-cholesterol in mmol/L, mean triglyceride in mmol/L), uric acid, NT-proBNP, kidney and liver parameters, CRP, vitamin D, TSH levels. HbA_1c_ testing was routinely done only upon admission (baseline).*

f
*Included 6-Minute Test Walk Distance (6-MWD), percent of predicted 6-MWD, Borg Rate of perceived exertion 1–10, saturation and heart rate after 6-Min walk test; functional independence measure (FIM), use of walking aids. Baseline and week 4 only: hand grip strength, state, and severity of general, physical (motor), and cognitive fatigue.*

g
*Included left ventricular mass index (LVMI), left atrial volume index (LAVI), global longitudinal strain average (GLS avg), end-diastolic volume (LVEDV).*

h
*Included measurement of the inferior vena cava (IVC) diameter at expiration and at maximum inspiration, collapsibility index of the IVC, assessment of sonography criteria of non-alcoholic fatty liver disease (NAFLD).*

i
*Included measurement of the muscle thickness ulna for the estimation of skeletal body mass in kg using muscle sonography (calculated as Muscle thickness ulna in cm × body height in m × 4.89–9.15), assessment of the pennate angle in degrees and echogenicity of the vastus lateralis muscle in arbitrary units, quadriceps muscle thickness.*

j *Included active monitoring for dehydration, polyuria, nocturia, urogenital infections, (euglycemic) diabetic ketoacidosis*.

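### Type 2 diabetes participants are split at 7 mmol/L on the same admission FPG that serves as baseline for their 4-week FPG change, so regression to the mean biases that change in opposite directions in Group I and in the diabetic part of Group II

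*Protocol article*

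**What the plan says.** The Study group categories section of the protocol article places T2D participants in Group I if they have "mean FPG of ≥7 mmol/l within the first 3 days upon admission under other standard of care medication"; they start an SGLT2i afterwards. Group II holds T2D participants "with mean FPG <7 mmol/L; and participants with impaired fasting glycemia (IFG) or pre-diabetes, defined as mean FPG of 5.6–6.9 mmol/L" (with an HbA1c range as well for this second set). Group II is therefore a mixture of T2D and pre-diabetes.

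The aims at the end of the Introduction include, for Group I, "to investigate the changes in physical performance and glycemic control 4 weeks after initiation of guideline-directed medical therapy of an SGLT2i and exercise therapy" and, for adequately controlled T2D, "the changes in physical performance and glycemic control 4 weeks after exercise therapy only in patients".

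The glycemic measure followed over time is found in the footnotes to Table 1: "mean fasting plasma glucose (for all groups at baseline, for group I and II at week 2 and 4". The same footnotes say of HbA1c that "testing was routinely done only upon admission (baseline". On timing, the outcome section says "Outcome assessments were done upon admission (baseline), facultatively at week 2 and at week 4".

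Data analyses sets the model time points at baseline and week 4. It names t-tests, repeated-measures ANOVA and linear mixed models; the listed adjustment variables do not include baseline FPG. The Discussion names selection on glycemic control as an important threat to interpretation, but does not mention regression to the mean.

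**The concern.** FPG varies from day to day, and these patients come from an acute hospital stay, so some of an admission value may be temporary. A patient on the high side of 7 mmol/L is more likely than not to have been measured above his or her usual level, and a patient on the low side below it. On remeasurement both move back. If the change is counted from the value that sorted them, this movement enters the result as change in glycemic control: a fall under SGLT2i plus exercise, and a rise under exercise alone. Averaging over up to 3 days shrinks the effect but does not remove it. None of the listed analyses separates it from a real change. At stake is how the FPG part of aims 1 and 2 can be read.

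**Working it through.** The plan states no figure to reproduce, and it gives no mean, SD or within-person variation for FPG. The direction follows from the design; the size needs assumptions.

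**Taken from the protocol article:** cut-off c = 7 mmol/L; classifying value = mean over the first 3 days; change counted from baseline to week 4; no separate baseline FPG described.

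**Assumed for T2D participants:** stable FPG with mean μ = 7.5 and SD 1.8 mmol/L; daily SD 0.8, averaged over 3 days; a temporary admission component of SD t = 0, 0.5 or 0.8 that lasts all 3 days and is independent of week 4. No treatment or time effect.

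**Formulas.** The variance of the classifying value X is s² = 1.8² + t² + 0.8²/3, and its reliability is ρ = 1.8²/s². With a = (7 − 7.5)/s and p = P(X ≥ 7) = 1 − Φ(a):

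- expected change in Group I = −(1 − ρ) · s · φ(a)/p
- expected change in Group II T2D = +(1 − ρ) · s · φ(a)/(1 − p)

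For t = 0: s² = 3.24 + 0.213 = 3.453, s = 1.858, 1 − ρ = 0.0618, a = −0.269, φ(a) = 0.385, p = 0.606. Group I: −0.0618 × 1.180 = −0.073. Group II T2D: +0.0618 × 1.815 = +0.112.

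| t | ρ | Group I | Group II T2D | Difference |
|---|---|---|---|---|
| 0 | 0.94 | −0.07 | +0.11 | 0.19 |
| 0.5 | 0.87 | −0.15 | +0.23 | 0.39 |
| 0.8 | 0.79 | −0.27 | +0.41 | 0.68 |

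Simulation with 2 million draws agrees with these values to within about 0.01.

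**Other assumptions.** With mean 6.5 to 8.0, between-person SD 1.2 to 1.8, daily SD 0.5 to 1.0 and no temporary component, the signs are the same in every case. The difference is 0.07 to 0.43 mmol/L with 3-day means and 0.22 to 1.08 with a single value.

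**Pre-diabetes members of Group II.** They are chosen from a two-sided window (5.6 to 6.9), so their drift depends on where their own mean lies. With assumed means of 5.2 to 6.5 it runs from −0.48 to +0.08 mmol/L and is usually slightly downward. With 3-day means and an assumed pre-diabetes mean of 5.5 or 6.0, Group II as a whole still rises unless this stratum makes up more than about 41% to 88% of it. Its share is not stated.

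**Check of a remedy.** Regressing week-4 FPG on the classifying FPG plus a group indicator gives a null group effect of about 0 in all three scenarios, because the expected week-4 value is linear in the classifying value under these assumptions.

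**The case against.** Four points on the other side have weight.

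- **Scope.** FPG change is not a primary outcome. Participants are not selected on 6-minute walk distance, percent predicted distance or Borg rating, so a reader who infers that the main comparison is biased by this mechanism goes beyond the documents. Glycemic change is stated as a within-group aim; a Group I versus Group II test of FPG is not explicitly planned. This stands and limits the point.
- **Caveats already given.** The Discussion says that the non-randomized design precludes causal conclusions and names selection on glycemic control. One therefore cannot say that the authors will credit the drug with a fall in FPG. But the caveat is general: it gives neither the direction nor the size of this bias, and it corrects nothing.
- **Size.** It is tempting to say that a null comparison at 130 per group would be significant 63%, 91% or 99% of the time. Those rates assume that nobody's true FPG changes over 4 weeks and that all of Group II has T2D. If true change varies between people with SD 1.0 or 1.5 mmol/L, the first rate falls to 24% or 15% and the second to 62% or 42%. The documents support no particular false-positive rate.
- **Group II.** A rise in the whole group does not follow, because of the pre-diabetes members. It follows for the T2D members, who are the subject of aim 2.

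**Conclusion.** The concern holds for FPG change in T2D participants. For them the grouping value and the starting value are the same measurement, as far as the article describes it, so a fall in Group I and a rise in Group II T2D are expected with no effect of SGLT2i or exercise whenever FPG varies within a person. The signs are secure as a contribution to the observed change. A common trend, such as recovery from acute illness, could add to or mask either one.

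The size is not known from the documents. Under the main assumptions it is about −0.07 to −0.27 mmol/L in Group I and +0.11 to +0.41 in Group II T2D; most of the range comes from how large a temporary admission component one assumes. The point limits what aims 1 and 2 can say about glycemic control. It does not touch the primary outcomes by this route.

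**What to change.** Data collection is complete, so the change concerns analysis and reporting only.

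1. Keep the groups as treated. Label the raw pre-post FPG change descriptive and do not read it as an effect of SGLT2i or exercise.
2. Where daily admission values exist, estimate within-person variance. Report the expected regression-to-the-mean shift for the T2D participants of each group beside the observed change. Call it a minimum, because a disturbance lasting all 3 days does not show up in day-to-day variance.
3. For any Group I versus Group II comparison of FPG, restrict to T2D participants and model week-4 FPG on the admission FPG used for grouping plus a group term (regression-discontinuity form). Check linearity on both sides of 7 mmol/L.
4. Name regression to the mean in the limitations.

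Reclassifying on earlier days with a later day as baseline is not a sound substitute. In simulation it leaves differences of about 0.20 and 0.50 mmol/L when the temporary component has SD 0.5 or 0.8, and about 5% of participants no longer match the treatment they received. Keeping the actual groups and taking day 3 as baseline removes nothing.

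The cost is a weaker statement about change in glycemic control, reliance on the functional form near the cut-off, and wider intervals. Under the t = 0 assumptions the correlation of admission FPG with group is 0.385/√(0.606 × 0.394) = 0.79, so the standard error of the group term grows by about 1/√(1 − 0.62) = 1.6.
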